### Safety

The following table provides the definitions used in safety reporting (Table 4):

**Table 4 Tab4:** Definitions used in safety reporting

Term	Definition
Adverse event (AE)	Any untoward medical occurrence that impacts the intervention, day to day activities, or requires medical intervention in a participant or clinical trial participant administered an intervention which is not necessarily caused by or related to that product
Serious adverse event (SAE)	Any adverse event that - · Results in death · Is life-threatening* · Required hospitalisation or prolongation of existing hospitalisation** · Results in persistent or significant disability or incapacity · Consists of a congenital anomaly or birth defect · Other medically important condition***
Serious adverse reactions (SARs)	Any SAE occurring in a clinical trial participant for which there is a reasonable possibility that it is related to the intervention
Suspected unexpected serious adverse reactions (SUSARs)	A SAR, the nature and severity of which is not consistent with the Reference Safety Information (RSI) for the intervention

*The term ‘life-threatening’ in the definition of serious refers to an event in which the trial participant was at risk of death at the time of the event or it is suspected that used or continued use of the product would result in the subjects death; it does not refer to an event which hypothetically might have caused death if it were more severe

**Hospitalisation is defined as an inpatient admission, regardless of the length of stay, even if the hospitalisation is a precautionary measure for continued observation. Pre-planned hospitalisation, e.g. for pre-existing conditions which have not worsened, or elective procedures, does not constitute an SAE

***other events that may not result in death, are not life-threatening, or do not require hospitalisation, may be considered as an SAE when, based upon appropriate medical judgement, the event may jeopardise the participant and may require medical or surgical intervention to prevent one of the outcomes listed above

For the purposes of this trial, incidences of self-harm are also considered SAEs. The frequency (percentage) of adverse and serious adverse events will be tabulated overall and by trial arm and compared using a chi-square test.

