## Methods

### Trial design

Full details of the SCHEMA trial design, setting, intervention, outcomes, and ethical approvals have been published in the protocol [12]. However, we provide a summary here as follows. The trial is a multicentre, two-arm, parallel-group, single-blind, individually randomised controlled trial (RCT) of effectiveness, comparing manualised interpersonal art psychotherapy to usual care. The RCT is being conducted in 8 NHS Trusts with secure care facilities and aims to recruit 150 participants (75 per trial arm). The total trial duration is 43 months with 20 months of recruitment. The end of the trial is defined as the last participant’s last visit [12].

The intervention arm is scheduled to receive 12 (1 h each) individual interpersonal art psychotherapy sessions, delivered by a trained HCPC registered art psychotherapist, plus usual care. Participants can receive up to 3 additional sessions throughout the trial for more personalised support, adjusting for the participant’s specific communication or therapeutic needs. The sessions cover the following 7 components: (1) personal goals, (2) coping responses and self-management, (3) relationships, (4) life events, (5) interpersonal themes, (6) imagined future and (7) final review. Participants will be considered as having completed the intervention if they complete at least 5 out of the 7 components listed above.

The control arm is scheduled to receive usual care, and participants are assessed and treated by specialist professionals. The multi-disciplinary team includes psychiatrists, clinical and forensic psychologists, mental health and ID nursing staff, and Allied Health Professionals. The team uses the Care Programme Approach to coordinate and plan participant care, including risk assessments, recovery-focused care and/or positive behaviour support [15]. Participants also have access to psychotherapy/psycho-educational work, specific offence-related treatment and pharmacotherapy treatment. Participants in the control arm are offered the art psychotherapy intervention at the end of their participation in the trial.

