### Randomisation

Participants were randomly allocated to receive either art psychotherapy plus usual care (UC) as the intervention arm, or UC with delayed art psychotherapy as the control arm. Participants were allocated to the intervention and control arm in a 1:1 ratio using randomly permuted blocks of 2, 4 and 6 created in Stata (version 17). This concealed allocation and minimised the predictability of the next allocation at the end of each block. Randomisation was stratified by sex and diagnosis of psychosis to achieve balance of baseline characteristics in the two groups.

The final randomisation list was generated by the senior statistician independently, keeping the trial statistician blind to the randomisation list. Randomisation took place online through the REDCap SCHEMA database and was available 24 h a day. Treatment allocations were automatically generated once the participant’s baseline data had been entered. As this is a single blind trial, the trial statistician, health economist and research support staff completing the primary outcome assessment are kept blind to allocation. For the statistical analysis, all data cleaning, manipulation, and analysis will be carried out by the trial statistician who will be kept blind to the arms allocation.

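### One of the three adverse event criteria applies almost only to the therapy arm, so the planned by-arm AE comparison can lean against art psychotherapy, by an unknown and possibly small amount

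*Protocol article*

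**What the plan says.** Table 4 in the Safety section defines an AE as "Any untoward medical occurrence that impacts the intervention, day to day activities, or requires medical intervention in a participant". The three consequences (on the intervention, on daily activities, need for medical care) are alternatives, so any one of them is enough.

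The same section states the analysis: "The frequency (percentage) of adverse and serious adverse events will be tabulated overall and by trial arm and compared using a chi-square test". Statistical principles treats p < 0.05 as statistically significant.

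Trial design says who receives the intervention: "The intervention arm is scheduled to receive 12 (1 h each) individual interpersonal art psychotherapy sessions". For controls: "Participants in the control arm are offered the art psychotherapy intervention at the end of their participation in the trial". Randomisation describes the arms as "art psychotherapy plus usual care (UC) as the intervention arm, or UC with delayed art psychotherapy as the control arm".

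The Safety section does not restrict the comparison to criteria that work alike in both arms. It does not separate events that qualify only through their effect on the intervention, and it attaches no caveat to the test.

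**The concern.** A between-arm comparison of AE percentages can be interpreted only if the same occurrence would be counted in either arm. Here one criterion depends on there being an intervention to affect. Suppose a minor medical occurrence leads to a cancelled art psychotherapy session, needs no medical care and leaves the rest of the day undisturbed. In the therapy arm it is an AE. In the control arm there is no art psychotherapy session to cancel, so it is not.

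The asymmetry arises when the event is classified. Randomisation does not remove it, and neither does the blinding of the trial statistician. It has one direction: events that qualify by this criterion alone add to the therapy arm. An apparent excess of AEs might then be read as harm, or a real reduction might be hidden.

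**Working it through.** **Inputs.** From the document: 75 participants per arm and 1:1 allocation (Trial design, Randomisation), chi-square test (Safety), 5% level (Statistical principles). The document gives no AE rate, so there is no figure of the plan to reproduce. Assumptions:

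- The test compares the proportion of participants with at least one AE.
- There is no true difference between arms on the two neutral criteria (daily activities, need for medical care), and the risk on these is 20% in both arms.
- An extra share d of the therapy arm has an AE through the intervention criterion only.

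**Method.** Let X ~ Bin(75, 0.20 + d) in the therapy arm and Y ~ Bin(75, 0.20) in the control arm. The Pearson statistic without continuity correction is ((X − Y)/75)² / (p̄(1 − p̄)·2/75), with p̄ = (X + Y)/150. The probabilities of all pairs (X, Y) with a statistic above 3.841 and X > Y are summed exactly.

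| d (points) | Therapy vs control | P(significant excess against therapy) |
|---|---|---|
| 0 | 20% vs 20% | 2.5% |
| 1 | 21% vs 20% | 3.5% |
| 2 | 22% vs 20% | 4.8% |
| 3 | 23% vs 20% | 6.5% |
| 5 | 25% vs 20% | 10.9% |
| 10 | 30% vs 20% | 29.1% |
| 15 | 35% vs 20% | 54.0% |

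**Other base rates.** Let p be the neutral risk and q the share of the remaining therapy-arm participants whose only AE comes through the intervention criterion. The therapy-arm rate is then p + (1 − p)q. The two-sided false-positive rates at 75 per arm are:

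| p | q = 0 | q = 0.02 | q = 0.05 | q = 0.10 | q = 0.20 |
|---|---|---|---|---|---|
| 0.1 | 5.1% | 6.5% | 13.3% | 35.1% | 82.4% |
| 0.3 | 4.9% | 5.2% | 7.3% | 14.6% | 43.5% |
| 0.5 | 5.5% | 5.7% | 6.7% | 10.2% | 25.0% |
| 0.7 | 4.9% | 4.9% | 5.3% | 6.8% | 12.9% |

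The effect is largest when AEs on the neutral criteria are rare and fades when they are common. The q = 0 column shows that the test is close to its nominal level once only neutral criteria count.

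**Masking.** If the neutral risk were truly 15% with therapy and 30% in controls, the chance of a significant result in favour of therapy would be 60%. Adding 5 points to the therapy arm (20% vs 30%) lowers it to 29%, and adding 10 (25% vs 30%) lowers it to 10%.

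**The case against.** The strongest reply is that the intervention criterion may add very little.

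- **Overlap.** Only events that qualify through that criterion alone cause bias. An occurrence that stops someone attending a session will often disturb other activities or need medical care, and then it counts in both arms. For an inpatient, a session may itself be seen as part of daily life. Trial design says that usual care includes psychological, educational and offence-related work, so a control's missed session of that kind can also count as an effect on daily activities. This stands, and it is the main reason to expect a small effect. It does not remove the asymmetry, because the therapy arm has 12 to 15 additional sessions that can be affected.
- **Small exposure.** Fifteen one-hour sessions in 38 weeks are 15 of 38 × 7 × 24 = 6,384 hours, about 0.2%. This also points to a small effect. However, what enters the test is the share of participants with at least one such event over all their sessions, and the hours do not give that share.
- **Control-arm cases.** Withdrawal/follow-up lists removal of a control from the art therapy waiting list after a worsening of mental health. A control's delayed therapy can therefore be affected by a medical occurrence. A reader might infer from Table 4 that controls can never meet the criterion; this entry shows that to be too strong. Such an event would very probably meet a neutral criterion as well.
- **Limited consequence.** AEs are neither a primary nor a secondary outcome, the article attaches no decision rule to the test, and Ethical approval describes a low-risk trial with steering committee review of safety data. This stands and limits the importance of the point.

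**Conclusion.** The concern holds in a limited form. As written, Table 4 contains a criterion that applies almost only to the therapy arm, and the Safety section tests AE percentages between arms without allowing for it. Any bias from events that meet this criterion alone runs against art psychotherapy.

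Two stronger readings are not supported. The first is that the therapy arm must show materially more AEs. That depends on how many events meet only this criterion, and the document gives no information on the number. With 75 per arm and a 20% neutral risk, 1 to 3 extra points move the chance of a significant excess against therapy from 2.5% only to 3.5–6.5%. The larger probabilities (11% to 54%) need 5 to 15 extra points. The second is that the SAE comparison is distorted too. The seriousness criteria and the rule that self-harm counts as an SAE do not depend on arm, so that comparison is largely unaffected.

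The change is still worth making. It is cheap, and without it a reader of the final report could not tell a modest AE excess from an effect of the definition.

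**What to change.** Leave the definition used for safety reporting as it is and change only the comparison. The between-arm AE table and test should count events that meet at least one arm-neutral criterion: effect on day-to-day activities, need for medical intervention, or seriousness. Events that qualify solely because they affected an art psychotherapy session should be listed descriptively for the therapy arm, with no between-arm test. No event is then lost from reporting.

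The classification rule should be fixed before the by-arm AE results are seen. Someone other than the blinded trial statistician should apply it, because an entry that mentions an art psychotherapy session reveals the allocation. The AE form is not shown, so the log may not record which criterion each event met. Where it does not, the event should stay in the comparison and the report should state the limitation.

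The cost is a short addition to the plan, one classification pass by a person outside the blinded analysis, and a slightly smaller comparative AE count.

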### Timing of outcome assessments

Outcome assessments (Table 2) are conducted at baseline (prior to randomisation), 19 and 38 weeks post-randomisation with a ± 2 weeks window.

**Table 2 Tab2:** Schedule of enrolment, interventions, and assessments

Procedures	Screening	Baseline	Randomisation	Treatment phase	19 weeks	Weekly	38 weeks	Ad hoc
Informed consent	X							
Eligibility assessment	X							
LDSQ	X							
Treatment allocation			X					
Demographics		X						
Medical history		X						
Q1 HONOS (WAA or LD)	X							
Randomisation		X						
Delivery of intervention				X				
Compliance				X				
MOAS		X			X	X	X	
EQ-5D-3L self-reported LD adapted version*		X			X		X	
EQ-5D-3L Proxy Version 1		X			X		X	
Resource use					X		X	
ReQoL-10 Self Report version		X			X		X	
ReQoL-10 Proxy reported**		X			X		X	
BSI		X			X		X	
Adverse event assessments								X
Physician’s withdrawal checklist								X

*LDSQ* Learning Disability Screening Questionnaire, *Q1 HONOS (WAA or LD)* Item 1 of the Health of the Nation Outcome Scale (Working Age Adults or Learning Disabilities), *MOAS* Modified Overt Aggression Scale, *BSI* Brief Symptom Inventory

*EQ-5D-3L self-reported using LD (learning disabilities) adapted version

**ReQoL-10 Self-Report version completed by a proxy

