### Primary outcome

The primary outcome is the frequency and severity of aggressive incidents as measured by the Modified Overt Aggression Scale (MOAS) at week 19 post-randomisation.

The MOAS is completed by a research nurse or clinical support officer at baseline (prior to randomisation), and weekly from week 19 to week 38 post-randomisation, and if necessary, checking with a member of the ward team to ensure that it accurately reflects the participant’s behaviour. The MOAS is not always completed by the same research nurse/clinical support officer, so we are recording who has conducted each assessment.

The MOAS is a validated observer-rated measure that assesses the frequency and severity of aggressive incidents among people with ID over the past week (ICC = 0.93 [16]). The scale consists of four categories: verbal aggression, aggression against property, auto-aggression (against self), and physical aggression (against others). Each category will be scored using a 5-point scale (0 = no events within that category, 4 = most severe form of aggression within the category). The rater selects as many items as are appropriate. The items in each category are summed. The summed scores are multiplied by the severity weight for that category (verbal aggression × 1, aggression against property × 2, auto-aggression × 3, physical aggression × 4). The weighted scores are summed to obtain the total MOAS score, with a higher score indicating more aggressive behavior [16]. Thus, the primary outcome is a change in the MOAS score from baseline to week 19 post-randomisation.

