#### Healthcare resource use and costs

Adults within secure care, such as the SCHEMA trial participants, have limited access to external health and social care services. As such, resource use for the trial analyses is limited to those healthcare resources that are recorded on the secure care electronic care systems for the trial participants. For example, this includes attendance at a special hospital, specialist assessment, and acute psychiatric ward admission, alongside specific staff contacts and medications. This healthcare data is collected by a combination of research staff and ward staff at 19 weeks and 38 weeks post-baseline. The resource use data is recorded within a proforma resource use measure (RUM) as part of the eCRF for the previous 19-week period since baseline or last RUM data collection time-point, i.e. each RUM is focused on the previous 19 weeks since the current point of data collection. The process involves research staff checking the patient notes for what resources the patient has used based on a proforma, which they then confirm with ward staff. As such, the healthcare data represents routinely recorded data for the trial participants, rather than self-reported, which avoids certain issues with self-reported data (e.g. recall measurement error or bias) [22]. The proforma RUM is presented within Appendix C. Through discussions with the SCHEMA TMG, RUM data is not collected at baseline to limit the data collection burden at baseline. Also, through TMG discussion, baseline resource use (i.e. resource-use consumption 19 to 38 weeks pre-baseline) was perceived not to be prognostic of resource use consumption (or other trial outcomes) over the proceeding 38 weeks post-baseline, limiting the use of baseline RUM data.

Unit costs are assigned to the resource-use information collected within the RUM to calculate total costs for each type of resource use and per trial participant [23]. Unit costs are sourced from data sources relevant to the NHS within England; this includes the National Schedule of NHS costs (e.g. for secondary care costs), Personal Social Services Research Unit (PSSRU) costs of health and social care (e.g. for staff costs), and British National Formulary (BNF; e.g. for medications) [24–26].

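### Self-harm counts as an SAE but no arm-neutral safety enquiry is scheduled before week 19, so the single pooled by-arm AE/SAE test may mix unequal ascertainment in weeks 1-18

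*Protocol article*

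**What the plan says.** All references are to the protocol article.

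- **Safety.** Self-harm is put among the serious events: "For the purposes of this trial, incidences of self-harm are also considered SAEs". The planned analysis is one comparison: "The frequency (percentage) of adverse and serious adverse events will be tabulated overall and by trial arm and compared using a chi-square test". No split by period is mentioned.
- **Timing of outcome assessments, Table 2.** The row "Adverse event assessments" is marked only in the ad hoc column. It has no mark under treatment phase, week 19, weekly or week 38. The scheduled visits are few: "Outcome assessments (Table 2) are conducted at baseline (prior to randomisation), 19 and 38 weeks post-randomisation".
- **Primary outcome.** The MOAS has four categories: "verbal aggression, aggression against property, auto-aggression (against self), and physical aggression (against others"). It "assesses the frequency and severity of aggressive incidents among people with ID over the past week". After baseline it is taken "weekly from week 19 to week 38 post-randomisation".
- **Trial design.** The therapy arm is scheduled for 12 individual one-hour sessions, with up to 3 more during the trial. Controls receive usual care and are offered the therapy when their participation ends.
- **Healthcare resource use and costs.** At weeks 19 and 38, in all participants, the notes are reviewed for the preceding 19 weeks: "The process involves research staff checking the patient notes for what resources the patient has used based on a proforma". The stated purpose is resource use, not adverse events.

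**The concern.** A by-arm comparison of event counts is fair only if an event has the same chance of entering the trial record in both arms. From week 19 the schedule supports this, because everyone has the same weekly MOAS. Before week 19 it does not ensure it. No safety enquiry is scheduled for either arm, while one arm meets a trial therapist individually and repeatedly. The Randomisation section lists who is kept blind to allocation, and therapists are not on that list.

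If the sessions bring self-harm or other events to the trial's notice, equal true rates could appear as an excess on therapy, and a real reduction in self-harm could be partly hidden. Self-harm also overlaps the primary outcome through the auto-aggression category, so a distorted safety table would affect how the main result is read. In addition, a rise in recorded self-harm after week 19 could partly reflect the start of weekly rating.

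**Working it through.** **1. Scheduled ascertainment by period (Table 2, Trial design, Primary outcome)**

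| | Weeks 1-18 | Weeks 19-38 |
|---|---|---|
| AE assessment, both arms | ad hoc | ad hoc |
| MOAS auto-aggression, both arms | none | weekly |
| Scheduled trial sessions, therapy arm | 12, up to 15 if the extra sessions fall here | none required by the plan |
| Scheduled trial sessions, control arm | 0 | 0 |

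The weeks without scheduled rating of self-harm are 18 of 38 (18/38 = 47%). The MOAS looks back one week, so the week-19 rating cannot recover the earlier weeks.

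**2. No stated figure to reproduce**

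The article gives no AE or SAE rate and no detection rate. From the documents come 75 per arm (Sample size), the 5% level (Statistical principles) and the chi-square test (Safety). Everything else below is assumed.

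**3. Effect if detection differs only in weeks 1-18**

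Assume a true participant-level risk of 30% over 38 weeks in both arms, with constant hazard.

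- Risk in weeks 1-18: 1 - 0.70^(18/38) = 0.155
- Risk in weeks 19-38: 1 - 0.70^(20/38) = 0.171
- Recorded risk with early detection s and full detection later: 1 - (1 - 0.155 s)(1 - 0.171)

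The rejection rate is found by exact enumeration of the uncorrected Pearson chi-square at 75 per arm.

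| Early detection, control v therapy | Recorded risk, control v therapy | Risk ratio | Rejection at nominal 5% |
|---|---|---|---|
| 100% v 100% | 0.300 v 0.300 | 1.00 | 4.9% |
| 90% v 100% | 0.287 v 0.300 | 1.04 | 5.2% |
| 80% v 95% | 0.274 v 0.294 | 1.07 | 5.7% |
| 70% v 95% | 0.261 v 0.294 | 1.12 | 7.1% |

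**4. How far this depends on the assumptions**

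Take a higher risk, 20% in each period, with full detection in the therapy arm. The recorded therapy risk is 1 - 0.8 × 0.8 = 0.36. With 60% early detection in controls, the control risk is 1 - (1 - 0.12) × 0.8 = 0.296. The risk ratio is 0.36/0.296 = 1.22 and the test rejects 13% of the time. With 90% or 80% control detection it rejects 5.5% or 6.9%.

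**The case against.** The strongest reply is that the setting works against the mechanism. Every participant in both arms is a secure-care inpatient, under a multidisciplinary team that carries out risk assessments, with electronic care records. Self-harm on such a ward would usually be noticed by ward staff whatever the allocation, and at most 15 hours of therapy adds little to that. Ad hoc can simply mean reported when it occurs. The full protocol, not shown here, may name one source of event reports for both arms, and an article may fairly leave that detail to it. All of this stands, and it limits the point to a risk.

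Three stronger readings are tempting and are not supported:

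- **That ascertainment is in fact unequal.** The article does not say that therapists report events, that sessions ask about self-harm, or that MOAS scores feed the SAE log.
- **That the distortion is large.** Applying the same detection gaps to the whole 30% risk would give risk ratios of 1.11, 1.19 and 1.36 and rejection of 6.9%, 9.6% and 18.7% (normal approximation). That treats the gap as lasting 38 weeks, whereas the schedule is the same in both arms from week 19.
- **That self-harm should be compared only in weeks 19-38, where scheduled ascertainment is matched.** That would leave out the treatment period, when harm from therapy matters most.

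The reply does not remove the point itself. The article fixes the self-harm rule, the ad hoc schedule, the MOAS timing and the pooled test, and that combination has no arm-neutral safety enquiry before week 19.

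**Conclusion.** The point holds as a risk: the pooled by-arm comparison of AEs and SAEs may mix unequal ascertainment in weeks 1-18. The documents do not show that it does, and they give no figure from which to size it. Under the main illustration, which rests on assumed risk, constant hazard and assumed detection rates, the apparent risk ratio is 1.04 to 1.12 and the false-positive rate about 5.2% to 7.1%. Detection close to equal would make the effect negligible; a much wider gap would make it larger. This is a cheap improvement to a secondary safety comparison, and it leaves the primary analysis untouched.

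**What to change.** 1. Report AEs and SAEs by arm for weeks 0-19 and weeks 19-38 separately as well as overall, with self-harm on its own line.
2. Base the by-arm self-harm comparison over the full 38 weeks on one source applied identically in both arms: extract self-harm from the patient notes already reviewed for resource use at weeks 19 and 38.
3. Cross-check every weekly MOAS auto-aggression score above 0 against the SAE log.

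**Cost.** The period split and the cross-check need no new data. The extraction takes some extra time and would be largely retrospective. Trial status gives plan approval on 04/02/25 and the last follow-up on 12/04/2025 (± 2 weeks). Nineteen weeks before 12/04/2025 is about 30/11/2024, so the week-19 reviews should already have been due when the plan was approved. Each period will also contain fewer events, so the period tables are better read as description than as separate tests.
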